### Objectives and outcome measures

The primary objective of this study is
**t**o identify candidate biomarkers associated with the rate of pleural fluid accumulation in patients with MPE and to use these biomarkers to develop and validate a clinical score to predict rate of reaccumulation. These biomarkers will be measured at day 0. This will be compared with the rate of pleural fluid accumulation based on increased size of pleural effusion from CXR immediately post-aspiration to day 7
^
12
^.

*Complete list of candidate biomarkers to be assessed for the primary objective*

The candidate biomarkers include:

Patient biomarkers: i) duration of symptoms; type of malignancy; ii) known malignancy or first presentation; iii) severity of pre-procedure breathlessness (measured on visual analogue scale); iv) previous chemotherapy and/or radiotherapy and/or immunotherapy; v) current chemotherapy and/or radiotherapy and/or immunotherapy; vi) current use of diuretics; emergency (
*via* Accident and Emergency (A&E) or acute medical unit) or urgent presentation (
*via* General Practice (GP) or oncology); vii) performance status (assessed using Eastern Co-operative Group scale); and viii) co-morbidities (chronic renal failure, liver disease, cardiac failure).Effusion biomarkers: i) size of effusion on pre-procedure CXR (measured as percentage opacification of hemithorax - this is a validated measure of effusion size); ii) size of effusion on pre-procedure US (measured from hemidiaphragm to top of effusion); iii) side of effusion; iv) volume of fluid drained during therapeutic aspiration (ml); v) degree of pleural fluid septations (categorised as none, mild, moderate or severe) on US; vi) significant non-expandable lung on post-procedure CXR; and vii) pleural pressures measured by manometry (substudy in 20 patients only in Norwich).Pleural fluid biomarkers: i) total protein; ii) pH; iii) glucose; iv) lactose dehydrogenase (LDH); and v) cytology (categorised as positive
*i.e.*, malignant cells present or negative).Serum biomarkers: i) haemoglobin; ii) white cell count, including neutrophil and leukocyte subsets; iii) C reactive protein; iv) total protein; v) estimated glomerular filtration rate (eGFR); vi) LDH; and vii) N-terminal pro-brain natriuretic peptide (NT-proBNP).

**
*Why were these biomarkers chosen?*
**

Duration of symptoms, underlying diagnosis and pre-procedure breathlessness were common factors identified by our clinician survey as being important in estimating how quickly pleural fluid will recur. Current treatment may reduce how quickly an effusion recurs. The co-morbidities specified are all associated with the production of pleural fluid, which may increase the rate of reaccumulation (despite the main cause being malignancy). Pre-procedure size of effusion was identified on two previous retrospective cohort studies as being associated with the need for a further pleural procedure, and we are measuring this in three ways (on X-ray, US and volume fluid drained). Septations are fibrin or collagen walls that develop within the effusion and impair drainage, and therefore may influence rate of reaccumulation. Non-expandable lung is defined as failure of the lung to re-expand following therapeutic aspiration and will be visible on the post-procedure CXR. It is associated with significant negative pressure within the pleural space, which may drive rapid pleural fluid reaccumulation. pH, LDH and cytology have been identified in previous studies as being associated with the need for a further pleural procedure. Total protein determines whether an effusion is an exudate or transudate and therefore is an important variable determining the mechanism of pleural fluid production. LDH has been identified as a variable associated with poor prognosis in patients with MPE. Haemoglobin, neutrophil: leukocyte ratio and C reactive protein have been shown to be associated with prognosis in patients with MPE. NT-proBNP is a measure of cardiac function and eGFR is a measure of renal function, so these variables may affect pleural fluid reaccumulation. High pleural fluid pressures may be associated with a strong drive to produce pleural fluid and hence rapid reaccumulation. These candidate biomarkers will be assessed to see which are appropriate for further analysis, based on our ability to detect variability within these measurements. If required, principal component analysis will be used to reduce the number of variables to eight for further analysis.

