**Methods:**

A total of 200 patients with known or suspected MPE attending for therapeutic aspiration will be recruited from 5–10 UK hospitals over 20 months. Patients will be enrolled prior to undergoing aspiration. Following this, they will undergo chest X-ray, which will be repeated one week later (treatment as usual). Rate of reaccumulation will be calculated based on change of size of the effusion seen on X-ray. Data will be collected on common clinical biomarkers
*e.g.*, size of effusion on pre-aspiration chest X-ray, volume of fluid drained. This data will be analysed to create a clinical score.

A further validation cohort of 40 patients will be enrolled in parallel with creation of the score.

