### Baseline assessments

The following baseline assessments will be made:

Clinical characteristics: duration of symptoms; Eastern Cooperative Oncology Group performance status (ECOG PS)
^
14
^; underlying diagnosis, current treatment of effusion
*e.g.*, chemotherapy for cancer, presence or absence of contralateral effusion.Baseline visual analogue scale for dyspnoea (VASD) (can be found as
*Extended data*
^
13
^).Blood samples will be taken and stored (optional long-term storage for future analysis - in selected sites depending on resources available).Baseline QoL questionnaire (EQ-5D 5L)
^
15
^

Patients will then undergo therapeutic aspiration, according to the standard operating procedure. Pleural manometry may be performed during aspiration using bespoke equipment with a manometer integrated in the therapeutic aspiration sheath (supplied by Rocket Medical, optional substudy of 20 patients in Norwich only).

Pleural fluid will be sent to local laboratories for microscopy and culture, cytology, total protein (TP), LDH, pH and glucose. These samples are all part of standard clinical care.

In addition, pleural fluid samples may be stored locally (optional long-term storage for future analysis - in selected sites depending on resources available).

Participants will then have a post-procedure CXR (as standard care) and thoracic US (as a study procedure) to assess size of residual effusion and presence of trapped lung, which will be recorded on the Case Report Forms (CRFs) (for later subgroup analysis) (can be found as
*Extended data*
^
13
^).

Following discharge, they will complete the seven-day VASD questionnaire (7DVQ) over one week on paper: this is a seven-day questionnaire in which patients assess their average level of breathlessness on a visual analogue scale daily.

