### Follow-up visits

**Day seven:** follow-up visit seven days after the therapeutic aspiration (can be done 5–10 days). This is part of standard clinical care for patients to receive results of pleural fluid testing and decide a management plan. Patients standardly have a CXR at this visit and this will be used to reassess size of effusion. At the point, the 7DVQ will be collected and a CRF completed, particularly to assess whether participants have required further pleural fluid drainage or attended the hospital with breathlessness during the seven-day period. During this period the participant is permitted to have any clinically required intervention.
**Second pleural procedure:** this will be performed if clinically indicated for diagnostic or symptomatic reasons. Indications for symptomatic drainage are as follows: symptomatic benefit from initial pleural fluid drainage; significant breathlessness; and significant pleural effusion (defined as at least 25% of the hemithorax on CXR or estimated volume of pleural fluid of at least 500 ml using US). Participants will undergo a further pleural drainage (
*via* thoracoscopy, chest drain or indwelling pleural catheter insertion according to clinical requirement in their individual care pathway). Patients will undergo CXR and US at this visit prior to intervention.
**Day 30:** follow-up by telephone/review of hospital records to determine further pleural procedures, emergency hospital attendances, other treatment for effusion
*e.g.*, chemotherapy, surgery, diuretics.
**Three months:** follow-up by telephone/review of hospital records to determine further pleural procedures, emergency hospital attendances, other treatment for effusion
*e.g.*, chemotherapy, surgery, diuretics. We will also collect health related QoL data using the EQ-5D 5L questionnaire by telephone.

Research staff will informally assess capacity at each follow-up visit. If the investigator believes that the participant has lost capacity to consent, no further data will be collected, and they will be withdrawn. The study data and samples will be used/retained if the participant had consented for this during the initial consent process.

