### Statistics and data analysis

**
*Description of statistical methods*
**

Reporting will include the number of patients screened for inclusion, the number of participants completing the study and exploratory analysis of any correlations between baseline factors and change in size of effusion on CXR.

*

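### The primary 'rate' has no stated time unit despite a 5–10 day follow-up window, and the post-aspiration size it starts from is missing from the candidate predictors

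*Protocol article*

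**What the plan says.** All references are to the Protocol article.

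- **Outcome.** Objectives and outcome measures gives the target as the "rate of pleural fluid accumulation based on increased size of pleural effusion from CXR immediately post-aspiration to day 7". The abstract (Methods) says: "Rate of reaccumulation will be calculated based on change of size of the effusion seen on X-ray". Statistics and data analysis speaks of "exploratory analysis of any correlations between baseline factors and change in size of effusion on CXR". The section on assessing effusion size on CXR says that opacification is measured on the post-procedure and follow-up films. None of these gives a time unit.
- **Window.** Follow-up visits defines the day-seven visit as a "follow-up visit seven days after the therapeutic aspiration (can be done 5–10 days").
- **Predictors.** Objectives and outcome measures introduces its list as the "Complete list of candidate biomarkers to be assessed for the primary objective". The list has pre-procedure size on CXR and ultrasound, and volume drained. The only item it takes from the post-procedure film is "significant non-expandable lung on post-procedure CXR". Effusion size after drainage is not listed.
- **Residual size.** Baseline assessments has a post-procedure CXR and ultrasound "to assess size of residual effusion and presence of trapped lung, which will be recorded on the Case Report Forms (CRFs) (for later subgroup analysis").
- **Planning figures.** Sample size and analysis plan assumes 150 analysable patients, R² 0.5, 8 parameters, and an outcome mean of 14 and SD of 13.

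**The concern.** A rate needs a denominator. If the outcome is the plain difference between films, two patients accumulating at the same speed get different values because one was seen on day 5 and the other on day 10. That is avoidable noise in the variable the score is built to predict. It would also enter the 40-patient validation cohort. If visit day is related to how fast fluid returns, the noise could become bias.

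The second part concerns the starting value. The outcome is follow-up size minus post-aspiration size, so measurement error and incomplete drainage in the first film enter the change with a negative sign. Adjusting for the baseline value is the usual way to remove whatever variance this creates. Pre-procedure size, volume drained and non-expandable lung are only partial substitutes for it.

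**Working it through.** **1. The plan's own figures.** With n = 150, p = 8 and R² = 0.5:
- Apparent R² = (0.5 × 141 + 8)/149 = 0.527, an optimism of 0.027 (plan: within 0.05).
- Shrinkage = 1 + (p − 2)/(n ln(1 − 0.527)) = 0.947 (plan: 0.95).
- Residual-SD margin, from chi-square limits on 141 degrees of freedom: 13.2% (plan: 13%).
- Half-width for the mean = t × 13 × √0.5/√150 = 1.48 (plan: 1.5).

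All of these reproduce.

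**2. What scale is the mean of 14 on?** It cannot plausibly be per day: 14 × 7 = 98 points of opacification in a week, with SD 13 × 7 = 91. It is a change over about a week. That fits a raw difference. A change scaled to 7 days would have the same units, but the article does not describe one.

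**3. The window.** Assuming linear growth, expected change is 14 × days/7:
- day 5: 10 points
- day 7: 14 points
- day 10: 20 points

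**4. Effect on R².** Write the 7-day change as L + e, where L is the predictable part. The mean is 14, and L and e each have variance 169/2 = 84.5. Let D be the visit day, unrelated to the predictors. The observed change is (L + e) × D/7, and a model that ignores D has

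R² = [84.5 × E(D)²/49] / [365 × E(D²)/49 − 4 × E(D)²], where 365 = 169 + 14².

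- Visits even over days 5–10: E(D) = 7.5 and E(D²) = 355/6 = 59.17, so 97.0/215.7 = **0.45**.
- Half on day 7 (10, 15, 50, 10, 5 and 10% on days 5 to 10): E(D) = 7.15 and E(D²) = 52.85, so 88.2/189.2 = **0.47**.
- 70% on day 7, 6% on each other day: E(D) = 7.18 and E(D²) = 52.66, so 88.9/186.1 = **0.48**.
- If e does not grow with time, the same three patterns give **0.48–0.49**.

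A simulation of 2 million draws gave the same values. The visit-day distributions are assumptions, since the article gives none.

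**5. Sample size.** At R² = 0.45, apparent R² = (0.45 × 141 + 8)/149 = 0.480 and shrinkage = 0.94, still above 0.9.

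**6. Post-aspiration size.** Let its SD be s, the follow-up SD be f and their correlation be ρ. The SD of the change is held at 13, which fixes f. The correlation of the change with post-aspiration size is (ρf − s)/13.
- s = 12, ρ = 0.3: f = 9.76, correlation −0.70 (49% of variance).
- s = 8, ρ = 0.5: f = 15.0, correlation −0.04 (about 0%).
- s = 5, ρ = 0.7: f = 16.0, correlation +0.48 (23%).

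The SDs and correlations are assumptions. These are marginal shares, before allowing for the size and drainage variables already on the list.

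**The case against.** The main counter-argument is that a raw difference is inferred, not stated. The article says the rate is based on the change, which does not exclude dividing by days. The correlations in the statistics section are labelled exploratory. Handling an interval within a visit window is ordinary analysis-plan content. Elapsed days would be a denominator, so its absence from a list of day-0 biomarkers proves little. This stands as a limit: the finding is that the time unit is undefined where the window makes it matter, not that division by days has been ruled out.

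Several stronger readings are tempting, and the documents do not support them.

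- **Residual size is reserved for subgroups only.** The same sentence attaches the subgroup purpose to trapped lung, yet non-expandable lung is a listed candidate predictor. What holds is the absence from the list headed as complete.
- **Both missing quantities are already recorded.** This is explicit only for residual size. The interval should follow from the aspiration and film dates, but that is implied.
- **The fastest accumulators will be materially under-read.** This could happen if they return early. But a fall in the mean of the fastest fifth from 32.2 to 26.1 points, for example, needs an average visit day of about 26.1/32.2 × 7 = 5.7 in that group, close to perfect ordering of visits by speed. Nothing in the article allows the effect to be sized.
- **Adding residual size removes 15–35% of the variance.** That is (1 − ρ)/2 for ρ from 0.7 to 0.3, and it requires equal SDs on the two films. If the post-aspiration SD is half the follow-up SD and ρ = 0.5, the gain is zero.
- **Without the covariate, the model cannot say whether an effusion will reach 25% of the hemithorax.** After aspiration the residual size is known, so adding the predicted change gives the predicted size.

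Finally, the Anticipated impact section foresees use of the prediction in place of a first aspiration. No residual size exists at that point, so for that use its omission is no defect. The candidate list does, however, already include volume drained and post-procedure lung expansion, so a post-aspiration model is clearly contemplated.

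**Conclusion.** The concern holds in a limited form. The outcome is called a rate but described only as a change between two films, over a window that doubles from its shortest to its longest interval, with no stated scaling or adjustment. Followed as written, this costs about 0.01 to 0.05 of R² from a starting 0.50. The upper end requires visits spread evenly over days 5–10; values of 0.47–0.49 apply if most visits fall near day 7 or error does not grow with time. All of this assumes linear accumulation and timing unrelated to the predictors. The 150-patient target stands.

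The omission of post-aspiration size from the predictor list is clear from the text. Its cost could be nil or substantial, and the article gives no SD or correlation to settle it. This is worth correcting before analysis because the remedy is nearly free. It is not a threat to the study's viability.

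**What to change.** Define the primary outcome with its time unit: change in percentage opacification per day, or scaled to 7 days, using the actual dates of the two films. Alternatively, include elapsed days in the model and report predictions at 7 days. Confirm that both film dates are captured.

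Add post-aspiration CXR size to the candidate list as a pre-specified covariate in any model meant for use after aspiration, and count it within the 8 parameters. State that it does not apply to a score used before aspiration.

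The cost is a change of wording and one parameter of the budget for residual size. Entering elapsed days as a covariate, instead of as a denominator, would use at least one more. No extra patients, visits or measurements are needed, provided the film dates are available.

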## Protocol

### Study design

This will be an observational cohort study recruiting patients with a pleural effusion attending the pleural clinic at five UK hospitals for a therapeutic aspiration of their effusion for breathlessness relief.

1.
**Phase 1:** observational cohort study of 200 patients in five hospitals for initial data to identify baseline characteristics associated with rate of pleural fluid accumulation and develop a predictive score.2.
**Phase 2:** validation observational cohort study of 40 patients in the same five hospitals to validate the score: this will be done in parallel with the analysis of data from phase 1.

If the above two phases are successful, we will proceed to:

3.
**Phase 3:** a final observational cohort study of 200 patients in the same five hospitals using the score to demonstrate impact on breathlessness, emergency admissions, number of pleural procedures, quality of life (QoL) and health economic outcomes: this final phase will be funded separately.

This protocol is for the first and second phases of this study.

### Participant identification

**
*Study participants*
**

Patients with a pleural effusion attending the pleural clinic at five UK hospitals for a therapeutic aspiration of their effusion with known or suspected MPE.

*
**Inclusion criteria**
*

Participant is willing and able to give informed consent for participation in the study.Aged 18 years old or above.Diagnosed with pleural effusion on CT or US.Patient attending for therapeutic aspiration (large volume drainage) of their pleural effusion: there is no specific minimal pleural fluid volume, but this should be larger than required for diagnosis alone (typically 60 ml is taken for diagnostic purposes).Known or suspected malignancy as the underlying cause of the effusion.In the Investigator’s opinion, is able and willing to comply with all study requirements.

*
**Exclusion criteria**
*

The participant may not enter the study if any of the following apply:

Patients who are pregnant or lactating.Pleural infection or other condition requiring admission and chest drain insertion.Known transudative pleural effusion or pleural effusion clinically thought to be primarily due to cardiac, renal or hepatic impairment.

### Protocol procedures

See
Figure 1 for study flow chart.

**Figure 1. f1:**
[figure not shown]
Study flow chart. PIL, patient information leaflet; VASD, visual analogue scale for dyspnoea; EQ-5D, baseline QoL questionnaire; LDH, lactate dehydrogenase; TP, total protein; CXR, chest X-ray; US, ultrasound.

*
**Recruitment**
*

All patients attending the Pleural Clinic for a therapeutic aspiration of pleural fluid will be informed of the study when their appointment is booked and will receive a patient information leaflet (PIL) by post with their appointment letter. Those who are interested in participating will be asked to contact the study team to confirm that they wish to take part. If no response is received, patients will be approached prior to their fluid drainage procedure by a member of the study team to confirm if they wish to participate, either by telephone or when they attend pleural clinic.

*
**Screening and eligibility assessment**
*

Patients attending the Pleural Clinic for therapeutic aspiration will be screened by confirming they fulfil the inclusion criteria, able to attend the follow-up appointment in one week and are willing and able to give informed consent. Patients will already have had clinical information, blood tests, thoracic US and pre-procedure CXR performed as part of standard clinical care.

*
**Informed consent**
*

Patients interested in participating in the study will be contacted by a member of the study team prior to their drainage procedure, either by telephone or at the time of attending pleural clinic. They will be given a copy of the Participant Information Sheet (PIS) and Consent form. This will explain why we are doing the study and what it involves for them. The PIS states that the patient is free to withdraw at any time and this will not affect their medical care or legal rights. The PIS and Consent form used in this study can be found as
*Extended data*
^
13
^.

They will have as much time as they want to think about joining the study and the opportunity to ask the research team any questions. There is no minimum time for this.

The participant must personally sign and date the latest approved version of the Informed Consent form before any study specific procedures are performed. The person who obtained consent must be trained in Good Clinical Practice (GCP) and have been authorised to do so by the Chief/Principal Investigator and must sign and date the informed consent form.

We anticipate that participants may lose capacity during the study due to disease progression. On the consent form, participants will be asked if they are happy for the study team to retain and use the study data and samples collected up to that point.

### Baseline assessments

The following baseline assessments will be made:

Clinical characteristics: duration of symptoms; Eastern Cooperative Oncology Group performance status (ECOG PS)
^
14
^; underlying diagnosis, current treatment of effusion
*e.g.*, chemotherapy for cancer, presence or absence of contralateral effusion.Baseline visual analogue scale for dyspnoea (VASD) (can be found as
*Extended data*
^
13
^).Blood samples will be taken and stored (optional long-term storage for future analysis - in selected sites depending on resources available).Baseline QoL questionnaire (EQ-5D 5L)
^
15
^

Patients will then undergo therapeutic aspiration, according to the standard operating procedure. Pleural manometry may be performed during aspiration using bespoke equipment with a manometer integrated in the therapeutic aspiration sheath (supplied by Rocket Medical, optional substudy of 20 patients in Norwich only).

Pleural fluid will be sent to local laboratories for microscopy and culture, cytology, total protein (TP), LDH, pH and glucose. These samples are all part of standard clinical care.

In addition, pleural fluid samples may be stored locally (optional long-term storage for future analysis - in selected sites depending on resources available).

Participants will then have a post-procedure CXR (as standard care) and thoracic US (as a study procedure) to assess size of residual effusion and presence of trapped lung, which will be recorded on the Case Report Forms (CRFs) (for later subgroup analysis) (can be found as
*Extended data*
^
13
^).

Following discharge, they will complete the seven-day VASD questionnaire (7DVQ) over one week on paper: this is a seven-day questionnaire in which patients assess their average level of breathlessness on a visual analogue scale daily.

